## Abstract

**Background:**

This is a registered study protocol on a randomized controlled trial (RCT) testing an intervention aimed to improve men’s adherence to evidence-based guidelines on BRCA1/2 germline genetic testing. *BRCA1*- and *BRCA2-*associated Hereditary Breast and Ovarian Cancer Syndrome (HBOC) increases the relative and absolute risk of developing breast and ovarian cancer and, to a lesser extent, prostate and pancreatic cancer. Men face *BRCA*-related cancer risks as women do, although with a different magnitude, and they may also transmit the mutations to their children. Notwithstanding, men are under-tested compared to women and the communication is not tailored on their needs. The present RCT applies principles of the Health Action Process Approach (HAPA) in testing the psychological determinants of the men’s adherence to evidence based guidelines on BRCA1/2 germline genetic and testing the efficacy of two messages.

**Methods:**

A total of 264 participants will be involved, among the men’s relatives of women with verified germline mutations. The study entails a pre- post- evaluation with randomization of the participants in two conditions corresponding to the two messages.

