Furthermore, applying the Uncertainty Management Theory [48], a social psychological approach to uncertainty, Rauscher et al. [14] investigated how men with increased *BRCA*-related cancer risk approach the individual and familial uncertainty related to that pathogenic variant. Those qualitative results showed that men’s primary concern when managing *BRCA*-related cancer risks is the aversive consequences of the discovery of a germline mutation for their family [49]. Their focus on familial uncertainty management is maybe due to the difficulties encountered in the management of their own risk due to the lack of information and management options. In the end, the authors suggested that genetic counseling would benefit a family focus. Also, Hallowell and colleagues [50] highlighted the role of family members (mother, partner, or children) in men’s decision-making about BRCA testing. In particular, they showed how men’s decision to have genetic testing was influenced by the obligations perceived from family members, primarily their children.

Based on these premises, this study protocol proposes to test the effectiveness of two first-person gain-framed messages, one narrating a self-referred story and the other a family-referred story. The effectiveness will be measured in terms of one or both messages ability to predict the intention to undergo the genetic screening.

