### Study plan

The experiment conducted in the third phase will be a Randomized Control Trial with participants receiving one of the two conditions (i.e., self-referred narrative framed message, family-referred narrative framed message) and it tests the main hypotheses and research question of the study. Participants will answer several questions before and after the message/treatment exposure.

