#### Time 1 assessment

All participants will complete the T1 assessment, via an online survey which will be available for a two-week period. The T1 measures will include demographic, health status, risk perception, health risk aversion, and intolerance of uncertainty. After this evaluation, participants will be randomized and exposed to one message. A manipulation check, the evaluation of the perceived quality of the information presented on the messages, positive outcome expectations, action self-efficacy, benefit for genetic test will be then collected. The constructs of trust in doctors and health literacy included in the original study protocol approved by the Ethical Committee have been not integrated here.

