#### Intervention

Participants will be randomly assigned to two groups. Both groups receive a message in which the main character is a man who speaks in first-person. The character has a sister with a *BRCA* germline mutation. After this common introduction, the content of the messages becomes different.

Group 1 receives a self-referred narrative message in which the protagonist explains that he has decided to have a genetic test to discover BRCA germline mutation. He then explains the reasons why this decision is important to himself (e.g., implementing preventive behaviors) and what are the possible benefits for the individual (S1 Fig 1 in S1 File).

Group 2 receives a family-referred narrative message in which the frame is similar to the previous message, but the character this time explains what the benefits for his family are and why his decision to have a genetic test is important to them (S1 Fig 2 in S1 File).

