#### Time 2 assessment

The original study protocol approved by the Ethical Committee included a T2 assessment with questions on intention to undergo germline genetic testing and evaluation of the quality of the message content, and a subsequent (3–4 weeks later) T3 with coping self-efficacy, action planning, and coping planning. Since the HAPA model does not state that there should be a waiting time between the measurement of the intention and the coping/action planning, we collapse T2 and T3. Therefore, one-two weeks after the administration of T1, via an online survey, participants reply to questions on intention to undergo germline genetic testing, coping self-efficacy, action planning, and coping planning.

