#### Time 3 assessment

Starting from the end of T2 until 3 months later, data on action initiation will be collected (i.e., genetic test for *BRCA1/2* gene germline mutations).

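### The plan promises a pre-post evaluation and a verdict on each message, but intention is asked only after the message and every man receives one, so only the relative effect of the two messages can be estimated

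*Protocol article*

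**What the plan says.** Three places in the protocol article describe what the trial will deliver.

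- Abstract, Methods: "The study entails a pre- post- evaluation with randomization of the participants in two conditions corresponding to the two messages". The abstract's Background also speaks of testing the efficacy of the two messages.
- End of the Introduction's section on informing men's decision making: "The effectiveness will be measured in terms of one or both messages ability to predict the intention to undergo the genetic screening".
- Discussion: the research is said to inform on how effective the two messages are.

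The schedule is given under Method.

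- Time 1 assessment, before the message: "The T1 measures will include demographic, health status, risk perception, health risk aversion, and intolerance of uncertainty". Then: "After this evaluation, participants will be randomized and exposed to one message".
- Time 2 assessment, one to two weeks later: "participants reply to questions on intention to undergo germline genetic testing, coping self-efficacy, action planning, and coping planning".
- At T3, over the three months that follow, uptake of the genetic test is recorded.
- Intervention: "Both groups receive a message in which the main character is a man who speaks in first-person". One story concerns the man himself and the other his family. There is no third arm.

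The primary objective and hypothesis 5 compare the family-referred with the self-referred message. Statistical analyses assigns hypothesis 5 to an ANCOVA with message type as the only predictor of interest.

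**The concern.** A reader of the abstract would expect the main outcome to be measured before and after the message. A reader of the Introduction would expect a conclusion about each message taken singly. The schedule and the arms support neither expectation.

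What is at stake is the conclusion that can be drawn. If the family and self messages give similar intention scores, the trial cannot say whether both raised intention or neither did. If the family message scores higher, that shows it did better than the other message, not that it raised intention above where the men began. The Discussion addresses the findings to health care providers, policy makers and public health managers, who may want to know whether to use such a message at all. The design does not answer that question.

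**Working it through.** **1. What is measured on each side of the message**

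| Construct | Before message | After message |
|---|---|---|
| Demographics, health status, risk perception, health risk attitude, intolerance of uncertainty | T1 | not listed |
| Message quality, outcome expectations, action self-efficacy, perceived benefit | not listed | T1 after the message (Time 1 assessment), or under T2 measures (Measures) |
| Intention, coping self-efficacy, action and coping planning | not listed | T2 |
| Action (genetic test) | not listed | T3 |

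The Time 1 assessment and Measures sections place the second row differently, but both put it after the message. Intention is post-message in every description, including the ethics-approved version summarised under Time 2 assessment. No construct is listed on both sides.

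**2. What the design identifies**

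Let F and S be mean T2 intention under the family and self messages, B mean intention before any message, and C mean intention with no message.

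- F − S is estimable, by randomisation.
- F − B and S − B are not, because B is never measured.
- F − C and S − C are not, because no arm goes without a message.

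F − S = 0 fits both F = S > C and F = S = C. For action, one might take untested men as starting from zero, but test uptake that would have occurred anyway still cannot be separated from a message effect.

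**3. What a baseline intention score would add to the F − S comparison**

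Inputs from Sample size and power calculation: partial η² = .05, alpha .05, target power .70, 2 groups, 7 covariates, calculated N = 132, planned N = 264, and η² = .01 from the cited earlier study. A two-sided test is assumed.

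The method is the noncentral F test with f² = η²/(1 − η²), numerator df 1, denominator df N − 2 − 7 and λ = f² × N. For η² = .05, f² = .05/.95 = .0526.

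The plan's own figure comes first. These inputs give N = 120 for power .70, not 132. N = 132 gives λ = 6.95 and power .744. That mismatch is a separate matter and does not affect this point.

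Adding baseline intention divides f² by (1 − r²) and takes one more df, so the denominator df is N − 10. Here r must be the correlation between baseline and T2 intention that is left after the 7 covariates. The documents give no value, so r = .3 to .7 is assumed. The multiplier 1/(1 − r²) is 1.10 at r = .3, 1.33 at .5 and 1.96 at .7.

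| η² | N | Power without baseline | r = .3 | r = .5 | r = .7 |
|---|---|---|---|---|---|
| .05 | 132 | .744 | .783 | .855 | .956 |
| .05 | 264 | .960 | .973 | .990 | .999 |
| .01 (cited study) | 264 | .370 | .400 | .468 | .625 |

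These figures concern intention only and do not carry over to action.

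**The case against.** The strongest reply is that the trial is comparative where it counts. The primary objective, the primary hypothesis and the hypothesis 5 predictor all set family against self, and a randomised post-message comparison answers that without a baseline. The pre-post phrase can be read loosely in the light of the Study plan section: "Participants will answer several questions before and after the message/treatment exposure". That is what the schedule does, and no planned analysis uses change from baseline. The promise about one or both messages stands in the Introduction, not among the objectives. Any head-to-head trial leaves absolute effects open.

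Most of this stands. A reader might infer that hypothesis 5 itself cannot be tested; the documents do not support that. What does not stand is the defence of the wording. The abstract's phrase suggests a repeated outcome where none is repeated, and the Discussion returns to the effectiveness of the two messages.

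A reader might also infer that asking intention at T1 would show whether a message works. It would not. Change within an arm would mix the message with time, repeated asking and the invitation itself. A reader might further infer a large loss of precision. At the plan's own effect and planned sample, power is already .960. At the cited η² = .01, even r = .7 leaves power at .625, below the plan's .70 target.

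Finally, asking intention minutes before a persuasive message may prime men or anchor them on their first answer. That this happens equally in both arms does not rule out a smaller contrast, so leaving the items out is a defensible choice.

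**Conclusion.** The point holds as a mismatch between stated claims and design. Change in intention, and the effect of either message against no message, cannot be estimated at any sample size in this design. This rests only on the article's own schedule and arms. The family-versus-self comparison is valid and is not in question.

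The precision gain is a secondary matter and depends on r. It is useful at η² = .05 with N = 132 (.744 to .78-.96), small at η² = .05 with N = 264 (.960 to .97-.999), and not enough to reach the .70 target at η² = .01 with N = 264 (.370 to .40-.62). It assumes a two-sided test and r of .3 to .7 after the 7 covariates.

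**What to change.** **Wording (needed).** In the abstract, the end of the Introduction and the Discussion, limit the stated conclusion to the relative effect of the family-referred against the self-referred message. Remove or qualify the pre-post description, and the sentence about the ability of one or both messages. State that a null result for hypothesis 5 does not distinguish both messages working from neither working. This costs nothing and leaves the analysis unchanged.

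**Baseline intention (optional, separate).** Ask the same three intention items at T1 before randomisation, and enter the score as a covariate in the hypothesis 5 ANCOVA for intention. Label any within-arm change as descriptive, because it cannot be attributed to a message. The cost is three items in an existing online survey, plus possible priming or anchoring, which the team should weigh. The article says no data had been collected at preregistration, so the change was open at that stage.

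If the effect of a message in itself is wanted, a no-message or standard-information arm would be required. That is a different and larger trial.

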**Discussion:**

The expected results provide answers related to the impact of action self-efficacy, outcome expectancy (personal or familiar), risk perception, health risk aversion, intolerance of uncertainty, perceived barriers, and coping self-efficacy on informed decision-making. Data gathered from this study may inform health care providers, policy makers, and public health managers about the communication strategy for men and about the psychological variables influencing decision-making.

**Trail registration:**

**Name of the Registry:** Clinical Trials. **Trial registration number:**
NCT04683068. **Date of registration:** 16/12/2020. **URL of trial registry record:**
https://www.clinicaltrials.gov/.

## Introduction

As for other pathogenic gene mutations [1–3], germline mutations in *BRCA1*- and *BRCA2* genes (BReast CAncer 1 gene and BReast CAncer 2 gene) predispose carriers to an increased susceptibility in developing breast and ovarian cancer [4] but also prostate, pancreatic cancer and melanoma [5]. *BRCA1* and *BRCA2* germline mutations are inherited in an autosomal dominant manner; this means that offspring of an individual with a *BRCA1* or *BRCA2* germline mutation have a 50% chance of inheriting the variant [6, 7], and the same probability of passing it to the progeny. *BRCA1/2* mutations have no gender distinction [8], both men and women can inherit the mutation, although it exposes them to different risks.

Men with *BRCA1/2* mutations can incur a lifetime risk of up to 6.8 per cent for breast cancer, and between 6 and 15 per cent for prostate cancer [7, 9]. These risks are particularly higher when *BRCA2* gene is involved. However, men do not receive the same attention as women [10]. In particular women can be tested to search *BRCA1* or *BRCA2* unknown germline mutations, especially when suffering from breast and/or ovarian cancer, or to search known *BRCA1/2* germline mutations previously identified in the family (i.e., cascade screening). Instead men are mainly involved in cascade screening and, rarely, they are tested for *BRCA1/2* germline mutations [11]. Very recently, the guidelines of the National Comprehensive Cancer Network [12] have suggested to consider patients with pancreatic and prostatic cancers as eligible for genetic testing for BRCA germline mutations. However, such a recommendation is not yet routine for the test proposal.

Some socio-cultural aspects have been related to the men’s attitude toward *BRCA1/2* mutations and genetic testing. For example, Pritchard [13] suggested that *BRCA 1/2* mutations are generally associated with female gender. He also pointed out that the name of the associated Hereditary Breast and Ovarian Cancer Syndrome (HBOC) creates confusion since breast and ovarian cancers are considered a ‘female matter’ by layperson [13]. Similarly, others [14, 15] have found that fear of stigmatization is one obstacle for the men’s decision-making. To date, there are no studies, applying a strong theoretical rationale, that have systematically tested which are the psychological variables influencing men’s informed decisions for genetic testing, when facing *BRCA*-related mutations. Moreover, to the best of our knowledge there are no studies testing what is the better communication strategy to inform men’s decision-making. Therefore, the present study aims to fill these gaps with an experimental study with a longitudinal component. First, applying principles of the Health Action Process Approach (HAPA), a motivational inclined theory that explains changes in behaviors, will be tested what psychological determinants influence the decision to undergo a genetic test for a germline BRCA mutations. The role of intolerance to the uncertainty and the health risk attitudes will be explored. The HAPA model has been chosen because it is an evolution of the first stadial models of health psychology [16] and it assumes that individuals pass through qualitatively different stages of psychological elaboration when they have to adopt new health behaviors. The other aim of the proposed study is to test two different narrative messages in order to understand which is the most efficient in informing men’s decision-making.

### Principles of the Health Action Process Approach (HAPA)

According to the Health Action Process Approach [17] there are several variables involved in the implementation of new health behaviors. Specifically, it is possible to identify risk perception, outcome expectancies and action self-efficacy as predisposing factors that have an impact on the informed decision; this is considered the motivation phase, in which subjects begin to form an intention. In this model, the intention to perform a specific health behavior is considered as a middle-level mediator between the variables considered in the motivation phase and those in the volition phase.

Furthermore, according to this model, volition factors involve planning that is further specified as coping and action planning and coping self-efficacy. Volition factors are considered as being influential in the subsequent phase and they are the most proximal predictors to actual behavior decision. This second phase (i.e., the volition phase) should be subdivided in pre-action phase, in which the previous mentioned coping and action planning, and coping self-efficacy take place, and action phase, ending with a behavior.

This model was tested in several health contexts [18, 19], in particular for smoking behavior [17, 20, 21], physical activity [22, 23], dietary [24, 25] and also in cancer-related screening behavior [26]. Those studies demonstrated the efficacy of the theory in explaining the initiation and maintenance of such health preventive behaviors. Together with the principles of the HAPA model, the present study aims to understand whether other psychological factors may explain men’s decision making regarding genetic testing for *BRCA1/2* germline mutations [27]. For this reason, two attitudinal factors are examined: intolerance of uncertainty and health risk attitudes.

### Intolerance of uncertainty and health risk attitudes

When people face a potential threat for their health, one key element affecting their subsequent decisions and behaviors is how much they feel certain or uncertain regarding the threat. In our case, a man who is considering the possibility to undergo a genetic test for BRCA germline mutations is facing two different types of uncertainty. The first one is the proximal uncertainty due to the result of the genetic test itself. The second one is the distal uncertainty depending on the risk to develop a cancer if a germline mutation would be found. The intention to undergo a genetic test for a germline mutation may be, therefore, determined by the way in which the individual manages the uncertainty due to the discovery of a possible negative result (i.e., the presence of a mutation) and to the future consequences of the germline mutation [28].

Intolerance of Uncertainty (IU) is a trait characteristic of individuals who are not able to tolerate the aversive reactions triggered by a perceived lack of sufficient information or by an issue that can have more than one solution [29]. Individuals with low tolerance for uncertainty tend to perceive the threat as a source of discomfort and to react negatively to it [30]. Some studies investigated the relationship between intolerance of uncertainty (IU) and the attitude to undergo health monitoring, in particular cancer-related screening [31, 32]. In particular, Tan and colleagues showed that intolerance of uncertainty may function as an important determinant of anxiety among men pursuing active surveillance for prostate cancer [31]. One qualitative study in lung cancer screening decision-making showed that some participants sought to decrease uncertainty through lung cancer screening and, if needed, with additional testing; others declined the screening in order to avoid the uncertainty associated with undefined results [33]. Indeed, intolerance of uncertainty consists of two dimensions: the first one, the desire for predictability, is an active strategy to manage uncertainty that is perceived as intolerable and leads to search for as much information as possible about the threat to restore a balance. Rosen and colleagues [34] showed that high levels of IU were associated with an increase in health monitoring and screening; other studies suggested that searching for threat-related information may be driven by the desire to reduce uncertainty [35, 36]. The second one, called uncertainty paralysis, is configured as an avoidance strategy, and leads to inability to act because of the uncertainty [29].

Another construct related to the previous one, at least in the health framework, is the attitude toward health risk. In order to contrast the perception of significant uncertainty, people choose responses and act in a certain way, and this is defined as the personal attitude toward the health risk. In fact, people differ in their attitude towards health risks, and this affects decision making regarding preventive behaviors (e.g., screening, physical activity), and risky behaviors (e.g., surgery) [37]. Taken together all this evidence suggests that IU and health risk attitudes may play a role when a man is making a decision to undergo a genetic test to detect BRCA germline mutation because there are similar mutations in the family. Since men with *BRCA*-related cancer risks deal with probabilistic and complex information [38, 39], both of these attitudinal factors can have an effect on the implementation of health behaviors and therefore can influence the informed decision to undergo cascade screening for *BRCA1/2* mutations.

